**Self-reported data**			

Questionnaires			
Physical activity *IPAQ (short form) *[47]	✓	✓	✓
Anxiety & depression *HADS *[48]	✓	✓	✓
Quality of life *EQ-5D *[49]	✓	✓	✓
Dietary habits *DINE *[50]	✓	✓	✓
General self-efficacy *GSE*[51]	✓	✓	✓

**Other**			

Ambulatory activity	✓	✓	✓

Abbreviations: **FPG **(fasting plasma glucose); **HbA1c **(glycated haemaglobin); **HDL **(high density lipoprotein cholesterol); **NS-SEC-5-Class **(National Statistics Socio-economic Classification 5-Class version); **IPAQ **(International Physical Activity Questionnaire); **HADS **(Hospital Anxiety & Depression Score); **EQ-5D **(EuroQol EQ-5D questionnaire); **DINE **(Dietary Instrument for Nutrition Education); **GSE **(General Self Efficacy); **IMD **(Indices of Multiple Deprivation)

##### Randomisation

Following their baseline appointment, eligible volunteers were randomised to either the study intervention arm (routine care plus TRIMS group education programme) or control arm (routine care) using computer-generated block randomisation. The researcher who held the randomisation sequence had no involvement with the recruitment of participants or baseline data collection. Blinding of participants was not possible due to the nature of the study. Participants were informed of their group allocation by a letter sent in the post and volunteers GPs were also provided with this information. People in the intervention group were informed that they would be given their bio-medical results as part of the TRIMS education and the control group were asked to contact their GP if they wanted any information about their results.

###### Delivery of the TRIMS intervention

Intervention group participants were contacted by telephone within 1 - 2 weeks of their baseline assessment and invited to attend the TRIMS education programme within the following 2 months. The education sessions were held Monday to Saturday, at various local community venues and consisted of 6 hours of contact time spread over two 3 hour sessions, held approximately 2 weeks apart. Participants were also invited to bring a friend or relative for both social and practical support. Two trained educators ([name] plus another nurse or a dietician) facilitated the groups. The approximate proportions of the curriculum devoted to specific topics are outlined in Table 3. In addition to attending the initial group education, at 6 months people will be given the option of receiving additional support from an educator ([name]), via the telephone, to answer any queries and concerns and to help participants update their self-management education resources.

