## Methods

### Study design

The TRIMS study was designed as a single-centre, 2 arm, parallel, 12 month randomised controlled trial (RCT) that compared the effectiveness of structured group lifestyle education (intervention) with usual care (control). Prior to commencing the main trial, an in-depth development and feasibility phase was carried out to ensure that the design of the intervention was appropriate for people with MetS.

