#### 1. Development and feasibility phase

##### Curriculum development

We adapted an existing group lifestyle education programme (Let's Prevent) which was originally developed for people with pre-diabetes [23]. The style, content and process of this programme draw on a range of concepts from health psychology and education [24-26] (see Table 1) and its philosophy is centred on patient empowerment. The key nutritional and physical activity messages are based on evidence from previous diabetes prevention trials [27-29]. Permission to adapt the pre-diabetes programme was granted by the DESMOND collaborative [30]. Using this curriculum as a framework, the TRIMS curriculum was revised to make it more suitable for people with MetS, who may or may not be dysglycaemic, and include additional emphasis on management of cardiovascular risk.

**Table 1 T1:** Main theories underpinning the structured group education self-management approach

Theory	Key elements
**Common sense model**	People tend to conceptualise a health threat/problem according to 5 domains:
	Identity; Cause; Timeline; Consequences; Control/cure
	Important to elicit these beliefs as thought to influence coping and self-care behaviour
	Influenced by social and cultural factors
	Health information needs to be aimed at targeting all 5 domains. If not:
	Individual is likely to acquire the missing information from another source
	Risk of forming spurious health beliefs
	Could negatively impact subsequent coping behaviour

**Dual process theory**	Systematic processing of information is encouraged
	Individual's are encouraged to take an active role in their learning and work things out and ask questions
	The educator does not lecture or dictate but uses open questions to elicit information
	Active learning requires recipient to make more effort. However:
	Results in individual's making a stronger link between theoretical concepts and their personal situation
	Attitude change generally lasts longer when produced by systematic processing

**Social cognitive (learning) theory**	Behavioural change is influenced by an individual's:
	Sense of control or perceived self-efficacy
	Expectancies about outcomes of personal actions
	Social modelling of knowledge and competencies
	People learn from interaction with others.
	Helps a person to realise what they already know
	Cultivates new competencies
	Instils behavioural outcome expectations

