##### Sample size

The TRIMS study is powered to detect a between group difference of 30% in the proportion of people with prevalent MetS at 12 months (prevalence of MetS reduced to 60% in the intervention group and 90% in controls, alpha = 0.05, power = 0.80) and allowing 20% for loss to follow up, 80 participants were required in total, 40 people in each of the control and intervention arms. The power calculation was based on the results of the Oslo Diet and Exercise Study (ODES)[52] which achieved a difference of 55% between the diet and exercise group and the control group. With our less intensive group lifestyle programme a more modest difference of 30% was assumed.

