##### Data analysis

Continuous outcome variables were tested for normality and independent-sample t-tests or Mann Whitney-U tests were used to compare between group differences at baseline; chi-square tests were used to compare categorical variables. Baseline data entry was conducted blind to group assignment, and steps were taken to ensure that data analysis was blinded as far as possible. Analysis of follow-up data will be conducted on an intention to treat basis. The study groups will be compared with respect to proportions of subjects with MetS at 12 months using the chi-squared test, followed by logistic regression modelling to adjust for any substantial chance imbalance between the groups, including adjustments for gender and ethnicity. Further study outcomes will be compared using similar methods and linear modelling, as appropriate and 95% confidence intervals will be calculated for treatment effects, corresponding to the statistical testing. Significance will be assessed at the 5% level. PASW Statistics version 18.0 (SPSS Inc.) will be used to conduct all statistical analyses. Qualitative feedback collected in order to gauge the acceptability of the TRIMS programme will be analysed using a thematic approach including the use of charting [40] to collate the data.

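### Only the intervention arm is taught in groups, yet the sample size and the named analyses treat all participants as independent, so the stated 80% power assumes no clustering

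*Protocol article*

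**What the plan says.** All places are in the protocol article.

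- **Randomisation:** allocation is by individual, and controls have no group component: "eligible volunteers were randomised to either the study intervention arm (routine care plus TRIMS group education programme) or control arm (routine care".
- **Delivery of the TRIMS intervention:** the programme is taught in two 3-hour sessions. "The education sessions were held Monday to Saturday, at various local community venues", and two educators "facilitated the groups". One educator appears to be the same throughout; the second may be a nurse or a dietician. The number and size of groups are not given.
- **Curriculum development, Table 1:** under one of the three underlying theories, "People learn from interaction with others".
- **Sample size:** "prevalence of MetS reduced to 60% in the intervention group and 90% in controls, alpha = 0.05, power = 0.80", with 20% loss, giving 40 per arm and 80 in total. No group size, ICC or design effect appears.
- **Data analysis:** the arms are compared on "proportions of subjects with MetS at 12 months using the chi-squared test", followed by logistic regression adjusting for imbalances, gender and ethnicity. Other outcomes use similar methods and linear models. "Significance will be assessed at the 5% level". No group term, random effect or robust variance is mentioned.

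**The concern.** People taught together share sessions, a venue, at least one educator and each other. If some groups go better than others, outcomes within a group are correlated, and this happens in one arm only. That is a partially nested design. A chi-squared test or ordinary regression then understates the variance of the intervention-arm estimate.

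The size of this matters because the trial is small and the planned power leaves little margin. It is also not simply a detail left to a fuller document: the article prints the sample size and names the primary test, and both rest on independence.

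**Working it through.** **1. Reproduce the stated sample size.** Inputs from the Sample size section: 0.60 and 0.90, alpha 0.05 (taken as two-sided; the article does not say), power 0.80, loss 20%. The mean proportion is 0.75.

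n per arm = [1.96 × √(2 × 0.75 × 0.25) + 0.8416 × √(0.60 × 0.40 + 0.90 × 0.10)]² / 0.30² = (1.2002 + 0.4835)² / 0.09 = 31.5, rounded up to 32.

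32 / 0.8 = 40 per arm, 80 in total. This matches the article exactly with a design effect of 1. Power at 32 per arm is 0.806. Other versions of the formula do not give 32: with continuity correction 38, one-sided 25, unpooled variance 29.

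**2. Allow for clustering in the intervention arm only.** With m analysed participants per group, DE = 1 + (m − 1) × ICC, applied to that arm's variance.

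- Actual size of the nominal 5% test, with equal prevalence and equal arms: 2 × [1 − Φ(1.96 / √((1 + DE)/2))].
- Correct CI width relative to the planned one, at 60% v 90%: √[(0.24 × DE + 0.09) / 0.33].
- Power of a correctly sized test at 32 per arm: Φ[(0.30 − 1.96 × √(0.1875 × (1 + DE)/32)) / √((0.24 × DE + 0.09)/32)].

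**3. Assumed values.** The article gives neither m nor ICC. I assume taught groups of 5 to 10, which after 20% loss are 4 to 8 analysed (5 × 0.8 = 4; 10 × 0.8 = 8), and an ICC of 0.01 to 0.10.

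Worked case, m = 8 and ICC = 0.05: DE = 1 + 7 × 0.05 = 1.35. Size: 1.96 / √1.175 = 1.808, giving 7.1%. CI ratio: √(0.414 / 0.33) = 1.120. Power: (0.30 − 0.2300) / 0.1137 = 0.616, giving 0.731.

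| m | ICC | DE | Type I error | Correct CI wider by | Planned CI too narrow by | Power at 32 per arm | Total N needed |
|---|---|---|---|---|---|---|---|
| any | 0 | 1.00 | 5.0% | 0% | 0% | 0.806 | 80 |
| 4 | 0.01 | 1.03 | 5.2% | 1.1% | 1.1% | 0.800 | 84 |
| 4 | 0.05 | 1.15 | 5.9% | 5.3% | 5.0% | 0.773 | 88 |
| 4 | 0.10 | 1.30 | 6.8% | 10.4% | 9.4% | 0.741 | 94 |
| 8 | 0.01 | 1.07 | 5.4% | 2.5% | 2.4% | 0.791 | 84 |
| 8 | 0.05 | 1.35 | 7.1% | 12.0% | 10.7% | 0.731 | 96 |
| 8 | 0.10 | 1.70 | 9.2% | 22.8% | 18.6% | 0.666 | 110 |

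The two CI columns differ because a correct interval r times as wide means that the planned one is too narrow by 1 − 1/r; for example 1 − 1/1.228 = 18.6%.

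**4. Check by simulation.** Beta-binomial simulation of the uncorrected chi-squared test (32 per arm, prevalence 75%, m = 8) rejected in 5.2% of runs at ICC 0, 5.6% at 0.01, 7.3% at 0.05 and 9.6% at 0.10. The formula gives 5.0%, 5.4%, 7.1% and 9.2%. The simulated test is already slightly above 5% at ICC 0, so the rise due to clustering agrees.

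**The case against.** The strongest objection is that a material ICC is not shown. A reader might infer from the group format that type I error does exceed 5%. The documents do not support that as a fact. Allocation is individual, so if the programme changes nobody's outcome the test keeps its size, however people were grouped. Inflation needs effects that differ between groups around a zero average. At an ICC of 0.01 it is slight.

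A reader might also take shared learning to be the mechanism of the programme. It is one element of one of three theories in Table 1. The curriculum is written, goals and action plans are individual, one educator seems common to all groups, contact is 6 hours, and the outcome is a biomedical classification 12 months later, partly determined by medication. All of this could keep the ICC low. Nor do the documents say that there were only a few large groups: recruitment ran from November 2009 to July 2010 over 8 practices, which fits smaller groups too. Participants who never attended belong to no group, which dilutes clustering under intention to treat. If follow-up is better than planned there is also some reserve: 40 analysed per arm would give power of 0.888 without clustering.

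These arguments limit the size of the effect and rule out a categorical claim. They do not remove the point. The plan sets the ICC to zero without saying so, in a design where only one arm is grouped.

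**Conclusion.** The point holds in conditional form. The sample size and the named analyses assume independence, although one arm is taught in groups. If the within-group ICC is above zero, the planned interval is too narrow and power is below 80%; type I error is above 5% when effects vary between groups around a zero average.

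For 4 to 8 analysed per group and an ICC of 0.01 to 0.10, both assumed, type I error is about 5.2% to 9.2%, the planned interval is about 1% to 19% too narrow, and power is about 80% down to 67%. At ICC 0 there is no effect. Applying the design effect to both arms, as in a cluster-randomised trial, would overstate the problem, because controls are not grouped.

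This would not overturn a clear result, but it could change the reading of a borderline one. It deserves a change because that change is cheap and follow-up was still to come.

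**What to change.** **Data analysis section.** Record the education group of each intervention participant. Pre-specify an analysis of the primary and continuous outcomes that allows for clustering in the intervention arm only. Either of these would do, with a small-sample correction:

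- a partially nested model, with a random group effect in the intervention arm and with controls and non-attenders as singletons; or
- a cluster-robust variance.

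At the least, make it a sensitivity analysis reported beside the chi-squared result, together with the estimated ICC. It should not be a second test that must also be significant before an effect is claimed; that would cost power in a trial planned on about 64 evaluable people (2 × 32).

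**Sample size section.** State that 80% power assumes no clustering, give the expected group size, and show power over a range of ICCs, as in the table above. Enrolment is complete at 82, so this is for interpretation and not for resizing.

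**Cost.** A few sentences of wording, and group membership that should be recoverable from session attendance. There will probably be few groups, so the ICC will be imprecise and the intervals slightly wider.

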###### Primary and secondary outcomes

The primary outcome is reversal of MetS according to the IDF criteria in the intervention group compared to the control group, after 12 months of follow-up. Taking into account the ethnic diversity within our target population, the IDF criteria were chosen in preference to the National Cholesterol Education Panel (NCEP) definition due to the provision of ethnic specific cut points for waist circumference and central obesity (Table 5). Secondary outcomes compared at baseline versus 12 months, and for the intervention group versus the control group, see Table 4, include changes in: i) the prevalence of MetS according to NCEP criteria; ii) individual components of the MetS (fasting plasma glucose, triglycerides, high density lipoprotein cholesterol (HDL), blood pressure, waist circumference), and 2 hour glucose.

**Table 5 T5:** The International Diabetes Federation (IDF) and updated National Cholesterol Education Panel (NCEP) definitions of metabolic syndrome.

**NCEP (2005)**[37]	**IDF (2005)**[6] ESSENTIAL REQUIREMENT **Central obesity** **Waist circumference** >94 cm^† ^(males) >80 cm^† ^(females)
*ANY 3 out of the following 5* ↓	***+ ****ANY 2 out of the following 4* ↓
**1) Raised fasting plasma glucose:** ≥ 5.6 mmol/l*	**1) Raised fasting plasma glucose:** ≥ 5.6 mmol/l
**2) Raised triglycerides:**** ≥ 1.7 mmol/l and/or **3) Low HDL cholesterol:**** < 1.03 (males) < 1.29 (females)	**2) Raised triglycerides:** ≥ 1.7 mmol/l *(or specific treatment for)* and/or **3) Reduced HDL cholesterol** < 1.03 (males) < 1.29 (females), *(or specific treatment for)*
**4) Hypertension:**** Blood pressure ≥ 130/85 mmHg	**4) Raised blood pressure:** Blood pressure ≥ 130/85 mmHg (or treatment for previously diagnosed hypertension)
**5) Central obesity:** Waist circumference > 102 cm (males) > 88 cm (females)	
*Updated from the original NCEP 2001 definition *[5]: *previous fasting plasma glucose value (≥6.1 mmol/l) was updated to include a lower value; *** was updated to include drug treatment *.	*^†^Waist circumference ethnic-specific for Europid men & women; Waist circumference for South Asians (Chinese, Malay, & Asian Indian): ≥90 cm (males), & ≥80 cm (females)*.

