#### 2. The TRIMS randomised controlled trial

##### Participant recruitment

Local ethics and research governance approvals were obtained prior to conducting the main TRIMS RCT. General practices (in Leicestershire, UK) who were already taking part in local population based diabetes screening studies [41-43] were approached to participate. Potential participants aged 40 - 74 years, from volunteer practices, were then recruited by postal invitation using two different recruitment strategies. Firstly, eligible people identified as having MetS (International Diabetes Federation (IDF) definition [6]) according to their previous screening results, were sent a postal invitation via their GP. Secondly, people who had consented to be approached with details of other research studies, when they participated in a screening study, and who met the inclusion criteria were sent a letter of invitation by the principal investigator of the screening study. Exclusion criteria included previous history of T2DM or CVD; pregnancy and/or breast feeding; life-limiting terminal illness; lack of capacity to give informed consent; being housebound or residing in a nursing/care home; and inability to understand, speak and read English.

Respondents were asked to attend for an initial appointment having fasted overnight for at least 8 hours. Written informed consent was obtained from volunteers by a research nurse prior to carrying out any tests or measurements. Participants underwent a 75 g oral glucose tolerance test (OGTT) [44], and had additional demographic and bio-medical data collected in a standardised way, according to the schedule in Table 4. Data collected included measurements to confirm eligibility and MetS status; however, if relevant blood tests for glucose and lipids had been conducted for screening within the last 3 months these were not repeated and the initial screening values were used as the baseline values.

**Table 4 T4:** Data collection schedule and outcome measures

Collected by research nurse	Baseline	6 months	12 months
Bloods & biomedical data			
FPG	✓	✓	✓
2 hour glucose	✓	✓	✓
HbA1c	✓	✓	✓
Total cholesterol	✓	✓	✓
HDL	✓	✓	✓
Triglycerides	✓	✓	✓
Albumin:creatinine ratio (urine)	✓	✓	✓
Blood pressure	✓	✓	✓
Waist circumference	✓	✓	✓
Hip circumference	✓	✓	✓
Height	✓	✗	✗
Weight	✓	✓	✓
Medical history	✓	✓	✓
Current medication	✓	✓	✓
Smoking status	✓	✓	✓
Biomarkers			
Insulin, Hs-CRP, Adiponectin	✓	✗	✓
Demographic details			
Age	✓	✗	✗
Sex	✓	✗	✗

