According to pedometer measurements, the median number of steps/day for participants was 5762 (IQR 3365 - 8592). Self-reported time spent sitting was 300 mins/day (IQR 180 - 360). Dietary data indicated that 46% (n = 34) of people were classified as having a low fibre intake and 15% (n = 11) as having a high fat intake. The median number of portions of fruit, salad and vegetables consumed per day was 3 (IQR 2 - 4).

All participants had MetS according to the IDF definition: 31% (n = 25) met 3 criteria, 54% (n = 44) met 4 criteria, and 16% (n = 13) met 5 criteria. The MetS values for the individual criteria for BP, HDL and triglycerides were met by 80 - 90% of people. However, only 22 participants (27%), 12 (29%) intervention and 10 (25%) control, met the criterion for raised fasting plasma glucose. Overall, the prevalence of MetS according to the updated NCEP criteria[37] was 94% (n = 77), 93% (n = 39) intervention group and 95% (n = 38) control (p = 1.000).

Table 7 and Table 8 present the main variables related to MetS, according to gender and ethnicity respectively. Characteristics for most variables across the treatment groups showed no significant differences. However, mean waist size was smaller for females in the intervention (99 cm, SD ±11) versus the control (106 cm, SD ±12), borderline statistical significance (p = 0.055). According to ethnicity, HDL levels were significantly higher for WEs in the intervention versus the control (1.3 mmol/l, IQR 1.1 - 1.8, v.s 1.2 mmol/l, IQR 1.1 - 1.3, p = 0.015) and triglycerides levels were lower (1.4 mmol/l, IQR 0.8 - 1.9, v.s 1.7 mmol/l, IQR 1.4 - 2.2) although statistical significance was borderline (p = 0.053).

**Table 7 T7:** Measures related to metabolic syndrome by gender

Metabolic syndrome components	All		Intervention		Control		p value (I vs. C)	
	Male, (n = 36)	**Female**, (n = 46)	Male, (n = 21)	Female, (n = 21)	Male, (n = 15)	Female, (n = 25)	**Male**,	Female
**Waist circumference(cm)**	109.0 ± 8.7	102.8 ± 11.5	108.5 ± 7.6	99.2 ± 10.5	109.6 ± 10.3	105.8 ± 11.7	p = 0.669	p = 0.055

**Systolic BP (mmHg)**	134.9 ± 13.7	130.5 ± 16.6	135.3 ± 11.7	134.4 ± 14.8	134.3 ± 16.6	127.2 ± 17.5	p = 0.822	p = 0.140

**Diastolic BP (mmHg)**	86.3 ± 9.6	85.5 ± 9.6	86.1 ± 10.6	85.1 ± 9.0	86.6 ± 8.4	85.8 ± 10.2	p = 0.890	p = 0.783

**HDL cholesterol (mmol/l)**	1.15 [1.00 - 1.40]	1.20 [1.10 - 1.50]	1.20 [1.00 - 1.40]	1.30 [1.10 - 1.80]	1.10 [0.90 - 1.50]	1.20 [1.10 - 1.45]	p = 0.528	p = 0.238

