Around half of all participants were prescribed a statin and/or antihypertensive at baseline. However, this was similar for both intervention and control group participants. We acknowledge that compliance could change during the study period but this could be a possible benefit of the intervention. In addition, it is recognised that prescribing may change, including new prescriptions for lipid or blood pressure medication to those who were medication naïve at baseline. This would then result in no change in the appropriate MetS criterion. However, prescribing changes will occur in a "real world setting" and are likely to occur in both groups. We are recording prescription medications at baseline, 6 months and 12 months and we will also consider looking at prescription records at the end of the study. Furthermore, our planned analysis using multi-variable regression methods will allow us to consider adjustment for prescribed medication.

We recognise that the majority of previous epidemiological studies and clinical trials have used the NCEP definition [5,37] to identify MetS. However, bearing in mind the ethnic diversity in our study population, provision of ethnic-specific cut-off points for waist circumference and central obesity within the IDF definition [6] led to preferential selection of this definition for our trial. Additionally, secondary outcome measures for the study include the prevalence of MetS according to NCEP criteria at 12 months follow-up compared to baseline.

We acknowledge that our study excluded people who were unable to understand, speak and read English. However, our study population includes a subset of the SA population in the UK (English speaking people mainly of Indian origin), and overall 22% of participants were of SA ethnicity. Additionally, we took steps to address cultural needs, for example by including foods commonly eaten in the SA community. If the education programme is found to be successful we will consider adapting it for non-English speakers and ethnically diverse populations. However, we acknowledge that additional work would need to be conducted to test for transferability of the intervention to other settings and populations.

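### Secondary outcomes are framed as changes, including a within-arm baseline-to-12-month comparison, and the outcome's own baseline value is not fixed as a covariate in the between-arm analysis

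*Protocol article*

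**What the plan says.** Under Primary and secondary outcomes, the article introduces the secondary outcomes with "Secondary outcomes compared at baseline versus 12 months, and for the intervention group versus the control group, see Table 4, include changes in". It then lists NCEP-defined metabolic syndrome, the individual components (fasting glucose, triglycerides, HDL, blood pressure, waist) and 2-hour glucose. Two comparisons are therefore named: over time, and between arms.

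The Discussion describes the NCEP outcome by the time comparison alone: "secondary outcome measures for the study include the prevalence of MetS according to NCEP criteria at 12 months follow-up compared to baseline".

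Under Data analysis, the primary comparison is a chi-squared test, "followed by logistic regression modelling to adjust for any substantial chance imbalance between the groups, including adjustments for gender and ethnicity". For the rest, "Further study outcomes will be compared using similar methods and linear modelling, as appropriate and 95% confidence intervals will be calculated for treatment effects". No section names the outcome's baseline value as a covariate, and none rules it out.

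Two other statements bear on this. The Results text reports that "All participants had MetS according to the IDF definition". Participant recruitment says that recent glucose and lipid tests could be carried over from screening: "these were not repeated and the initial screening values were used as the baseline values".

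**The concern.** There are two separate issues.

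The first is the comparison over time. Entry required metabolic syndrome, and the baseline visit supplied measurements used to confirm it. For some participants the screening glucose and lipid values are themselves the baseline. Where a component was selected for being beyond a cut-off, its later values tend to drift back without any intervention. For NCEP status, 77 of 82 were positive at baseline, so prevalence has far more room to fall than to rise. A fall within the intervention arm is therefore not evidence that the programme works.

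The second is the contrast between arms. Randomisation makes a comparison of mean changes unbiased on average, but for the sample actually drawn it carries part of any chance baseline gap into the result. Adjustment depends on an imbalance being judged large, with no definition of large. The Results and the Discussion both already call the arms balanced on the ground that no overall difference was statistically significant. On that reasoning, the gaps in systolic BP and waist could go unadjusted. A baseline gap moves the estimate whether or not it is significant.

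**Working it through.** **Inputs (Table 6, intervention n = 42, control n = 40; 2-hour glucose 41 and 40).**

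- Systolic BP: 134.9 (SD 13.2) against 129.8 (SD 17.3); gap D0 = +5.1 mmHg.
- Waist: 103.9 (SD 10.2) against 107.2 (SD 11.2); gap = -3.3 cm.
- Diastolic BP: 85.6 against 86.1; gap = -0.5 mmHg.
- Fasting glucose: 5.23 against 5.19; gap = +0.04 mmol/l.
- 2-hour glucose: 5.65 against 5.95; gap = -0.30 mmol/l.
- Correlation r between baseline and 12 months: not in the article. Assumed 0.5 to 0.7, with 0.3 to 0.9 as a wider range.

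**The article's own figures.** The pooled SD for systolic BP is √[(41 × 13.2² + 39 × 17.3²)/80] = 15.3, so the gap is 5.1/15.3 = 0.33 SD, with t-test p = 0.136 (Table 6: 0.139). For waist the pooled SD is √[(41 × 10.2² + 39 × 11.2²)/80] = 10.7, so the gap is 0.31 SD, with p = 0.167 (Table 6: 0.161). Both agree with the table to within rounding of the summary statistics.

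**Offset of a change-score contrast.** Let D12 be the 12-month difference, intervention minus control. The change contrast is D12 - D0. With equal variances at the two times, the ANCOVA slope is r and the adjusted contrast is D12 - r × D0. The change contrast therefore differs from ANCOVA by -(1 - r) × D0.

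| Outcome | r = 0.3 | r = 0.5 | r = 0.7 | r = 0.9 | Direction |
|---|---|---|---|---|---|
| Systolic BP (mmHg) | -3.57 | -2.55 | -1.53 | -0.51 | favours intervention |
| Waist (cm) | +2.31 | +1.65 | +0.99 | +0.33 | against intervention |
| 2-hour glucose (mmol/l) | +0.21 | +0.15 | +0.09 | +0.03 | against intervention |
| Diastolic BP (mmHg) | +0.35 | +0.25 | +0.15 | +0.05 | negligible |
| Fasting glucose (mmol/l) | -0.03 | -0.02 | -0.01 | 0.00 | negligible |

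**Precision.** In units of 2σ²/n, the variance is 2(1 - r) for a change score and 1 - r² for ANCOVA. The ratio ANCOVA/change is (1 + r)/2: 0.75 at r = 0.5 and 0.85 at r = 0.7 (0.65 and 0.95 at the ends of the wider range). Inverted, 1/0.85 = 1.18 and 1/0.75 = 1.33, so change scores have 18 to 33% more variance. With the planned 20% loss, 40 × 0.8 = 32 per arm complete the trial. A change-score analysis of 32 is as precise as ANCOVA on 32 × 0.75 = 24 to 32 × 0.85 = 27.

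**NCEP status at baseline.** 39 of 42 and 38 of 40 were positive. That leaves 3 + 2 = 5 negative of 82, which is few for a covariate.

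**Primary outcome.** Every participant had IDF metabolic syndrome at baseline, so baseline IDF status cannot differ between arms. The sample size is not involved.

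**The case against.** The strongest reply is that the between-arm analysis is planned and baseline adjustment is left open. The opening sentence on secondary outcomes names intervention against control, and Data analysis promises linear models and intervals for treatment effects. Change can be the name of an outcome whose model still adjusts for baseline, and an article may leave its covariate list to an analysis plan not shown here. This largely stands. A missing covariate list alone would not be a finding. What remains is what the article does state: a comparison over time, outcomes expressed as changes, and adjustment triggered by an undefined degree of imbalance.

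A reader might infer more, and the article does not support it:

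- *That within-arm tests replace between-arm ones.* Both are named, and no within-arm result is offered as proof of effect. The Discussion sentence on NCEP is part of an explanation of the choice of definition.
- *That follow-up changes will be compared by t-test or Mann-Whitney according to a normality test.* That sentence concerns differences at baseline.
- *That regression to the mean biases the trial's treatment effect.* It acts equally on both randomised arms in expectation.
- *That every component must improve.* The lipid and blood pressure criteria also count treatment, and 51% took a statin and 51% an anti-hypertensive. Mean fasting glucose was 5.21 against a cut-off of 5.6, and only 22 of 82 met that criterion.
- *That the 90% assumed for controls, from 100% at entry, is regression to the mean.* The Sample size section gives no such reason.

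The reuse of screening values covers glucose and lipids only, so it does not bear on the systolic BP or waist figures.

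**Conclusion.** The point holds as a modest improvement to the analysis. It does not show that the planned between-arm comparison is invalid. Within-arm change cannot carry inference in a sample selected on the same measures. For the between-arm contrast, omitting the baseline value would shift systolic BP by about 1.5 to 2.6 mmHg towards the intervention and waist by about 1.0 to 1.7 cm against it, would leave diastolic BP and fasting glucose essentially unchanged, and would cost 18 to 33% in variance. These figures assume a correlation of 0.5 to 0.7, equal variances over time, and linear models that leave the baseline value out. If those models already include it, the offsets vanish and only the wording of the comparison over time needs attention. The systolic BP and waist shifts run in opposite directions, so no overall bias towards the programme follows. They are still a reason to settle the model before the follow-up data are seen.

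**What to change.** State in Data analysis that:

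1. Each continuous secondary outcome is analysed as the between-arm difference at 12 months, adjusted for that outcome's own baseline value whatever the observed imbalance, and reported with its 95% CI. Skewed measures such as triglycerides are analysed on the log scale.
2. NCEP-defined metabolic syndrome is compared between arms at 12 months, adjusting for baseline NCEP status where the model can be fitted. With only 5 of 82 negative at baseline it may not be, and the unadjusted between-arm difference with its interval should then be reported.
3. Baseline-to-12-month changes within each arm are descriptive only. The outcome description in the methods and the NCEP sentence in the Discussion should be brought into line with this.

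The cost is a change of wording. The data collection schedule already provides for every component at baseline and at 12 months, and neither the sample size nor the primary analysis changes.
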